#### Secondary objective

To determine whether additional immunohistochemical analysis on endometrial biopsies could predict recurrence and disease free survival. Additionally, to determine whether incorporation of abnormal cervical cytology and comorbidity attributes to an improved risk classification.

### Study design

Multicentre, prospective cohort study in nine hospitals in the Netherlands. From September 1st 2011 till December 1st 2013 all patients treated for EC in participating hospitals are included. Patients without preoperative histology, history of hysterectomy and/or endometrial carcinoma or no surgical treatment including hysterectomy are excluded. Patient characteristics, as well as comorbidity (Charlson index), BMI, family history of hereditary syndromes (BRCA1/2, Lynch syndrome), postmenopausal status and parity are registered. Based on the present comorbidities, all patients are assigned a comorbidity score based on the Age-Adjusted Comorbidity-index as described by Charlson et al. [31], with EC being excluded from the scoring. Treatment and final pathological diagnosis are registered as well as occurrence of recurrent disease during at least 24 months follow-up.

### Tissue specimens

The endometrial biopsy or curettage on which the diagnosis of EC was made will be used for systematic evaluation by pathologists with special interest in gynaecologic pathology. Additional IHC analysis of IMP3, p53, ER, PR, MLH1, PTEN, beta-catenin, p16, Ki-67, stathmin, ARID1A and L1CAM will be performed (Table 1). Final pathology will be reviewed by the expert pathologists and compared with the preoperative histological diagnosis. The pathologists will be blinded for clinicopathological information and outcome.

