### Preoperative diagnosis

During the last decades dilatation and curettage (D&C) has been replaced by minimally invasive techniques for endometrial sampling in an outpatient setting. The amount of tissue obtained from endometrial sampling is relatively small and there can be different subtypes of EC in one tumour, making routine histological discrimination between EEC and a high grade, UPSC or CCC difficult. Moreover, in 30 % the amount of tissue obtained with outpatient endometrial sampling is insufficient for diagnosis [12]. Previous studies found discrepancy percentages between 15 and 40 %, including both grade and histological subtype [13–17]. When preoperative diagnosis was based on D&C or endometrial sampling, a preoperative diagnosis of grade 1 was concordant with the final diagnosis in 85 % of cases. However, high grade lesions were more frequently underestimated by endometrial sampling compared to D&C [18].

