### Statistical analysis

For the primary objective, results of endometrial biopsy and curettage will be compared with final pathology results. Both univariate as well as multivariate analysis will be performed to determine whether immunohistochemical markers contribute to prediction of final pathology. For the secondary objective we will also include abnormal cervical cytology and the Age-Adjusted Comorbidity-index as factors in univariate and multivariate analysis. In order to determine risk factors for recurrence Kaplan-Meier survival curves will be calculated to determine outcome after a follow-up time of 24 months. Statistical analysis will be performed using the Statistical and Data management package SPSS 20.0.

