## Discussion

A total of 432 EC patients from nine hospitals were collected between September 2011 and December 2013. The inclusion of patients has finished and we are now analysing the data. Follow-up will be completed in December 2015. The various histological subtypes of EC are all represented in this study group with 86 % EEC, 8 % UPSC and 2 % CCC based on hysterectomy evaluation. This is in line with percentages reported in the Netherlands Cancer Registry [32]. Clinicopathological characteristics are shown in Table 2. Atypical hyperplasia is diagnosed in 13 % of the preoperative endometrial samples, where final diagnosis on hysterectomy was EC.

**Table 2 Tab2:** Clinicopathological characteristics of 432 women with endometrial carcinoma. Values are presented as median (range) or number (%)

Characteristics		
Age at primary surgery, years	66	(41–90)
Pre-operative histology^a^		
Office endometrial biopsy	311	(72.0)
Hysteroscopic biopsy	128	(29.6)
Curettage	75	(17.4)
Histological subtype^b^		
Endometrioid	370	(85.6)
Serous papillary	33	(7.6)
Clear cell	9	(2.1)
Mucinous adenocarcinoma	2	(0.5)
Carcinosarcoma	18	(4.2)
Histological grade^b^		
1	193	(44.7)
2	127	(29.4)
3	112	(25.9)
FIGO 2009 stage		
I	362	(83.8)
II	27	(6.3)
III	35	(8.1)
IV	8	(1.9)

^a^ 82 patients have more than one pre-operative histological sample

^b^ Unrevised classification based on hysterectomy specimen

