We will determine if a diagnostic panel of IHC markers can improve the preoperative diagnosis for risk selection. This is the first study combining L1CAM with other markers to find the optimal panel of biomarkers for the preoperative diagnosis of EC. The additional value of immunohistochemical analysis in EC has been demonstrated in the large multicentre MoMaTEC trial [20], yet, this study focussed on predicting lymph node metastasis and prognosis in relation to treatment. Our focus is on preoperative risk classification with respect to histological type and tumour grade. Preoperative and final surgical pathology will be revised by expert pathologists. Furthermore, preoperative biopsy and curettage will be evaluated systematically, and compared with final histology. Additionally, background endometrium will be classified as: atrophic endometrium, hyperplastic endometrium, normal proliferative endometrium or indeterminate. Since, in a previous study on hysterectomy specimens, atrophic background endometrium was found to be an independent prognostic factor for patients with grade 1 EEC [6]. To date, no studies on the prognostic value of background endometrium in preoperative endometrial sampling are published.

Due to tumour heterogeneity and focal staining patterns, IHC on endometrial biopsies may not always be representative for the whole tumour. Most studies on IHC in endometrial carcinomas were performed on hysterectomy specimens. Yet, our clinical challenge is to select high risk tumour preoperatively on a limited amount of material. Our study design represents daily practice and with this study we will determine whether additional IHC analysis could predict final histology. Huang et al. reported comparable sensitivity for detecting high grade EC with Pipelle versus curettage [33]. The predictive value between endometrial biopsies and curettage might be different when IHC is applied, and hence influence outcome. To date, there are no studies on the influence of IHC on the difference in predictive value between biopsy and curettage. By using IHC the difference in the amount of material collected by biopsy and curettage might become relevant. Interestingly, incorporation of comorbidity in the preoperative risk classification has not been studied so far.

Summarizing, systematic preoperative evaluation of both tumour and patient characteristics could give maximal information and result in patient tailored treatment in patients with EC.

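### The evaluated preoperative sample is chosen because it showed cancer, so agreement with final pathology leaves out non-diagnostic and hyperplasia-only samples

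*Protocol article*

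**What the plan says.** All references are to the protocol article.

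- **Study design** sets entry: "Patients without preoperative histology, history of hysterectomy and/or endometrial carcinoma or no surgical treatment including hysterectomy are excluded".
- **Tissue specimens** sets the sample: "The endometrial biopsy or curettage on which the diagnosis of EC was made will be used for systematic evaluation".
- **Statistical analysis**, for the primary objective: "results of endometrial biopsy and curettage will be compared with final pathology results".
- **Preoperative diagnosis** (Background) cites earlier work: "in 30 % the amount of tissue obtained with outpatient endometrial sampling is insufficient for diagnosis". For grade, "a preoperative diagnosis of grade 1 was concordant with the final diagnosis in 85 % of cases". It also cites overall discrepancy between 15 and 40 %.
- **Discussion** reports: "Atypical hyperplasia is diagnosed in 13 % of the preoperative endometrial samples, where final diagnosis on hysterectomy was EC". A footnote to Table 2 adds: "82 patients have more than one pre-operative histological sample".
- **Discussion** also states: "Our study design represents daily practice and with this study we will determine whether additional IHC analysis could predict final histology".

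**The concern.** A sample picked because it gave the cancer diagnosis cannot be a complete miss. Suppose a woman has an insufficient office biopsy and then a curettage showing carcinoma. She enters the cohort, but only the curettage is compared with the hysterectomy, and the failed biopsy counts nowhere. A woman whose sample showed only atypical hyperplasia has, on a literal reading, no sample to evaluate, yet her preoperative result understated the disease.

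Both omissions push agreement upward. The discordance between preoperative and final diagnosis is the problem the study sets out to reduce, so its baseline size matters. The tissue-amount assessment planned under Methods would also say little about how often sampling fails if it covers only samples that succeeded.

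The article is also inconsistent with itself: the Discussion counts hyperplasia samples among the preoperative samples, and the rule under Tissue specimens has no place for them.

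**Working it through.** **1. The article's own counts (Table 2).** Office biopsy 311, hysteroscopic biopsy 128, curettage 75.

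311 + 128 + 75 = 514, and 514 - 432 = 82. This matches the footnote if each of the 82 patients had two samples. 82/432 = 19.0 %.

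**2. Patients with hyperplasia only.** The 13 % is given per preoperative sample without a stated base. Assume the base is 432 patients and that none of them had another sample showing carcinoma.

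0.13 x 432 = 56.2, about 56; 432 - 56 = 376 remain.

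**3. Effect on agreement.** Let A be agreement among the 376. Each of the 56 is non-agreement by definition, because hysterectomy showed carcinoma. Agreement over all patients is A x 376/432. The article gives no A for this cohort. The values below are assumptions taken from its cited range (discrepancy of 15 to 40 %, so agreement of 60 to 85 %).

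| Assumed A in the 376 | Agreement in all 432 | Overstatement |
|---|---|---|
| 85 % | 0.85 x 376/432 = 74.0 % | 11.0 points |
| 60 % | 0.60 x 376/432 = 52.2 % | 7.8 points |

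The 85 % also equals the cited grade 1 concordance, a narrower quantity than agreement on type and grade together.

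**4. Failed first samples.** Let d be the number of patients, outside the 56, whose first sample was insufficient or non-diagnostic and who had a later diagnostic one. With A = 85 %, first-sample agreement over all patients falls by a further 0.85 x d/432, about 0.2 points per patient. The article does not give d. At d = 0 there is no further effect. The outer limit is d = 82, which assumes that Table 2 lists every sample and that every repeat followed a failure: 0.85 x 82/432 = 16.1 points. Nothing in the article supports that limit as an estimate. The cited 30 % insufficiency is not used here, because it is a literature figure and need not apply to women who have carcinoma.

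**The case against.** The strongest reply is that the main question concerns markers, and markers can be scored only where there is tumour tissue. **This stands.** Modelling on the diagnostic sample is a legitimate target and limits scope only.

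Second, the 13 % suggests that hyperplasia samples are in the data, so the rule may not be applied literally. **This stands in part.** The bias may not arise in practice, but the two statements still conflict, and an analyst following the written rule would drop these patients.

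Third, an insufficient sample gives no wrong class, so it is not disagreement in the usual sense. **This stands**, and is a reason to show insufficient results separately. It does not apply to hyperplasia, which is a result, and an underestimate.

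Fourth, a condensed article commonly leaves the handling of repeat samples to the full protocol. That would excuse silence. Here a rule is stated, and it selects on the outcome of sampling.

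Fifth, the sentence on daily practice follows a remark about working with little material rather than hysterectomy specimens. That is a fair reading, but the sentence is broader than the rule supports.

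Three stronger readings are tempting and **not supported**:

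- *A planned biopsy-versus-curettage comparison is flattered.* None is planned. The objectives do not contain one, and Statistical analysis compares sample results with final pathology, not with each other. The Discussion only raises the possibility of a difference.
- *All 82 repeat samples are discarded failures.* The footnote gives neither order, result nor reason. Both samples may have shown carcinoma, and the rule does not say which is then used.
- *Patients with a failed first sample leave the study.* They stay in through the later sample. Only patients with no preoperative histology are excluded.

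**Conclusion.** The concern holds as a bias in the planned agreement analysis and as a conflict between Tissue specimens and the Discussion. It does not invalidate the marker model. Under the stated assumptions (base of 432, 56 patients with hyperplasia only, 85 % agreement in the rest), agreement would be reported as 85 % instead of 74 %. At 60 % agreement in the rest, it would be 60 % instead of 52 %. The effect is smaller if some of the hyperplasia samples belong to patients who also had a cancer-positive sample, though those patients' first results may then be lost through the other route. The added effect of failed first samples cannot be sized from the article and may be nil.

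**What to change.** 1. Keep the diagnostic sample for the immunohistochemical modelling.
2. Reconcile Tissue specimens with the 13 % in the Discussion: state that hyperplasia-only patients stay in the agreement analysis and count as underestimates. Give the base of the 13 %.
3. Report adequacy and agreement also by sampling method on each patient's first preoperative sample. Show insufficient results separately and include them in the denominator.
4. State which sample is used when more than one showed carcinoma.
5. Describe panel performance as applying to patients with an evaluable tumour sample, and narrow the daily-practice sentence to match.
6. If biopsy and curettage are contrasted at all, note that curettage patients may be selected by a failed biopsy. Restricting the contrast to women who had both does not cure this, because a second sample taken after a failure selects against biopsy.

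The cost is modest. No extra staining is needed and the repeat samples are already counted in Table 2, but the routine reports of first samples must be retrieved where they are not already held. The agreement figure will be less favourable. According to the Discussion the data are already being analysed, so the rule should be settled before the agreement results are reported.

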### Methods

Tissue specimens are collected centrally at the department of Pathology, Radboud university medical centre in Nijmegen. Pre-operative samples will be evaluated on the amount of tissue (quantitatively and qualitatively), the presence of hyperplasia, atypia, endometrial intraepithelial carcinoma (EIC), invasive growth, background endometrium, tumour percentage and tumour type and grade. IHC staining will be performed on formalin-fixed, paraffin-embedded tissue of the pre-operative samples. IHC staining will be graded semiquantitatively by considering the percentage and intensity of the staining. A staining index will be calculated as the product of staining intensity and staining area.

### Statistical analysis

For the primary objective, results of endometrial biopsy and curettage will be compared with final pathology results. Both univariate as well as multivariate analysis will be performed to determine whether immunohistochemical markers contribute to prediction of final pathology. For the secondary objective we will also include abnormal cervical cytology and the Age-Adjusted Comorbidity-index as factors in univariate and multivariate analysis. In order to determine risk factors for recurrence Kaplan-Meier survival curves will be calculated to determine outcome after a follow-up time of 24 months. Statistical analysis will be performed using the Statistical and Data management package SPSS 20.0.

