### Sample size calculation

Calculation of the sample size is based on the primary outcome variable of the study, which is high risk endometrial carcinoma. The smallest outcome group, in this case patients with high risk endometrial carcinoma, should be 10–20 times the amount of independent variables used.

Independent variables in the analyses will be: age (dichotomous), grade (1, 2 and 3) and the best predictive immunohistochemical markers. For the sample size calculation we assume to include six immunohistochemical markers in the multivariate analysis. Grade count as two variables because we use it as a trichotomous variable, which makes the total variables nine.

The amount of subjects in the smallest group therefore should lie between 90 and 180. However, as a rule of thumb, the amount of subjects should never be lower than 100.

With an expected high risk endometrial carcinoma rate of 25 % at least 400 patients with endometrial carcinoma should be included to include at least 100 patients with high risk endometrial carcinoma.

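### Comorbidity is analysed through an index that contains age, and the only stated age term is dichotomous, so an age effect can be credited to comorbidity

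*Protocol article*

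**What the plan says.** Four sections of the Protocol article bear on this.

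- **Secondary objective:** the aim is "to determine whether incorporation of abnormal cervical cytology and comorbidity attributes to an improved risk classification". The question is about comorbidity, not about age.
- **Study design:** "all patients are assigned a comorbidity score based on the Age-Adjusted Comorbidity-index". One item is taken out of the score: "with EC being excluded from the scoring". Nothing says that the age component is taken out. The same section lists the Charlson index among the registered characteristics.
- **Statistical analysis:** for the secondary objective, "we will also include abnormal cervical cytology and the Age-Adjusted Comorbidity-index as factors in univariate and multivariate analysis".
- **Sample size calculation:** "Independent variables in the analyses will be: age (dichotomous), grade (1, 2 and 3) and the best predictive immunohistochemical markers". This is the only place where the coding of age is stated, and it gives no cut-point. It continues "we assume to include six immunohistochemical markers in the multivariate analysis" and, after counting grade as two, "which makes the total variables nine". Neither the index nor cytology is in that count.

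Table 2 gives age at surgery as median 66, range 41–90, so age is held in years.

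**The concern.** An index that adds age points to comorbidity points cannot, tested alone, separate the two. If older patients more often have high-risk disease, the index will tend to be associated with the outcome even when comorbidity plays no part.

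A multivariable model would repair this if age were modelled well. A two-level age term does so only partly. Within each age group patients still differ in age, the index still rises with age, and the index is then the term in the model that can carry the remaining gradient.

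At stake is one component of the secondary objective. The Discussion presents comorbidity in preoperative risk classification as unstudied, so a positive result would be read as new evidence about comorbidity when it might reflect age.

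**Working it through.** **The plan's own figure.** Age 1 + grade 2 + markers 6 = 9 variables; 9 × 10 = 90 and 9 × 20 = 180; floor 100; 100 / 0.25 = 400 patients. This reproduces. It confirms that age takes a single two-level term. It says nothing about how the index behaves, so that was examined by simulation.

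**Inputs from the article.** n = 432; age centred on 66 within 41–90; high-risk rate 25 %; index analysed alone and with other factors; age dichotomous.

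**Inputs assumed (not in the article).** Age normal with SD 10, clipped to 41–90. Age points A = one per decade from 50, at most 4. Comorbidity points C Poisson with mean 0.8. Age cut at 66. Two-sided 5 % tests. Age odds ratio (OR) per decade 1.0 to 2.0.

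**Model.** Index = A + C. Log-odds of the outcome = ln(0.25/0.75) + ln(OR) × (age − 66)/10. C has no effect on the outcome, so every significant result for the index or the score is a false positive.

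**Why a dichotomy is not enough.** Take two patients aged 67 and 85 with the same comorbidity. Both are in the upper age group, but their age points are 2 and 4. At an age OR of 1.5 per decade their true odds differ by 1.5^1.8 ≈ 2.1. The age term treats them as equal; the index does not.

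**False positives for comorbidity, 500 runs per row (%).** The last two columns use C alone, without age points.

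| Age OR per decade | C rises with age? | Index alone | Index + age cut at 66 | Index + age in years | C alone | C + age cut at 66 |
|---|---|---|---|---|---|---|
| 1.0 | no | 4.6 | 5.4 | 4.4 | 4.0 | 4.2 |
| 1.3 | no | 39.4 | 12.8 | 4.8 | 6.6 | 6.6 |
| 1.5 | no | 68.6 | 22.0 | 5.0 | 4.4 | 4.0 |
| 1.5 | yes | 79.6 | 25.0 | 5.4 | 12.4 | 6.6 |
| 2.0 | no | 97.8 | 44.4 | 5.4 | 4.0 | 3.4 |
| 2.0 | yes | 99.2 | 58.0 | 2.8 | 21.2 | 5.8 |

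Here yes means that mean comorbidity points are multiplied by e^0.2 ≈ 1.22 per decade. Simulation error (1 SE) is √(0.05 × 0.95/500) ≈ 1.0 point near 5 % and √(0.22 × 0.78/500) ≈ 1.9 points near 22 %.

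At OR 1.5 with C independent of age, the median OR per index point is 1.23 alone and 1.11 beside dichotomised age; the true value for comorbidity is 1.00. The index correlates about 0.72 with age, so age accounts linearly for about 0.72² ≈ 52 % of its variance.

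**Sensitivity.**
- Age cut at 60 or 70 (OR 1.5): 23.0 % and 16.6 % beside dichotomised age. Age points capped at 5 instead of 4: 22.2 %.
- Age OR of 1.03 or 1.05 per year (1.03^10 ≈ 1.34 and 1.05^10 ≈ 1.63 per decade), across sets of runs with differing assumed comorbidity means and event numbers: 23–88 % alone and 7–30 % beside dichotomised age. With the non-age score plus age in years: 3–6 %.
- Half the assumed age weight in the index: 13–47 % alone, 6–12 % beside dichotomised age.
- Grade added to the model (800 runs, assumed links from age to grade and from grade to outcome). With half of the age effect running through grade: 4–5 % at 1.03 per year and 7–9 % at 1.05. With all of it through grade: 5–6 %.

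**The case against.** **No age effect is given.** The article reports no association between age and high-risk disease or recurrence. A reader might infer that an age effect will be reported as a comorbidity effect. The text does not support that: with no age effect every version of the test stays near 5 %, and at 1.03 per year most simulated studies show no false positive beside dichotomised age. This stands, and the point is limited to what can happen.

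**The joint model is inferred.** Dichotomous age appears only in the sample size section, for the primary outcome, and the secondary model's other covariates are not listed. The words that the index is also included suggest that age carries over, but do not prove it. This stands as a limit on the multivariable figures. It does not remove the concern, because without an age term the result would move towards the univariate figures.

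**Counting age twice is not the fault.** A reader might infer that having age in both the index and a separate term is what does the damage. It is not: the index beside age in years holds about 5 %. The harm comes from the coarse age term and from the univariate test without age.

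**The simulated model is simpler than the planned one.** It leaves out the six markers and, except in the last check, grade. Only the age effect that remains after those terms can leak into the index. How much remains is unknown, so 7–30 % is nearer an upper range. Recurrence is to be described by Kaplan–Meier curves, which a logistic simulation does not represent.

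**A composite index is a fair predictor.** For prediction alone this is true. It does not show that comorbidity itself contributes, which is what the objective asks.

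**The scoring is not printed.** That age adds points is read from the index's name, and the points per decade are assumed. Halving the weight reduces the effect but does not reverse it.

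**Conclusion.** The concern holds in a conditional form. The objective is about comorbidity, the variable to be analysed is an age-inclusive index from which only endometrial carcinoma is removed, and the only stated age term has two levels. If age is related to the outcome, the univariate test of the index cannot answer the question, and the multivariable test can be partly an age test.

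For an assumed age OR of 1.03–1.05 per year and a null comorbidity effect, false positives are roughly 25–90 % univariately and 7–30 % beside dichotomised age. The second range may fall close to 5 % if grade and markers absorb most of the age effect. With no age effect both are about 5 %. The direction follows from the stated choices; the size rests on the assumed age effect, age spread, comorbidity distribution and index scoring. The point concerns one part of a secondary objective and does not touch the primary one.

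**What to change.** - Score comorbidity without the age points, with endometrial carcinoma still excluded.
- Enter age in years as its own term, and judge comorbidity's contribution from the multivariable model that contains it.
- Report univariate results for age and for the non-age score separately, as description. The non-age score tested alone can still be confounded if comorbidity rises with age (12–21 % in the table).
- Keep the Age-Adjusted index for describing the cohort only.

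The cost is small. The Charlson index is registered and age in years is available, so no new data are needed, and age and comorbidity still take one term each. The Discussion says inclusion has ended and analysis is under way, so the change should be dated and declared as made at that stage.
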